## Statistical plan for data analysis

### Adaptive design

Within the present study, an interim statistical analysis will be undertaken after the first 80 subjects have completed follow up. If a realistic extension to this study could achieve clinically and statistically meaningful conclusions regarding the primary outcome we will extend recruitment.

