## Estimated study start date:

First patient first visit: 28th November 2020

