## Estimated study completion date:

Last patient last visit: 28th February 2023

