## Study Design and Methods

### Methods

A randomised (1:1) pilot study of 120 consecutive consenting patients. The intervention group will undergo a comprehensive cardiac assessment and standardised treatment protocols will be followed to treat identified CVD. Patients will be followed for 12 months to gather outcome data. CVD is defined as hypertension, ischaemic heart disease (IHD), HFPEF, HFREF, atrial or ventricular arrhythmia, moderate-severe valvular heart disease or cor pulmonale.

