### Primary

1. The number of days spent alive outside of a hospital environment during 12 months post hospital discharge

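### The decision to extend recruitment falls 6 to 7 months after recruitment is due to finish, and its open criterion does not guarantee the error rate of the final test

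*Protocol*

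**What the plan says.** The Methods section describes "A randomised (1:1) pilot study of 120 consecutive consenting patients" and adds "Patients will be followed for 12 months to gather outcome data". The primary endpoint is "The number of days spent alive outside of a hospital environment during 12 months post hospital discharge". The anticipated enrolment rate is 7 to 8 patients per month. The planned dates are "First patient first visit: 28 th November 2020" and "Last patient last visit: 28 th February 2023".

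Under Adaptive design, "an interim statistical analysis will be undertaken after the first 80 subjects have completed follow up". The action that follows is: "If a realistic extension to this study could achieve clinically and statistically meaningful conclusions regarding the primary outcome we will extend recruitment".

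Under Outcome measurements, the primary outcome is compared between groups by Student's t-test or the Mann-Whitney U test. The Power calculation section gives no effect size, standard deviation or significance level.

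**The concern.** There are two difficulties, and the first is the firmer.

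**Timing.** An interim analysis that may enlarge a trial is useful while patients are still being enrolled. Here the trigger is 80 completed 12-month follow-ups in a trial that plans only 120 patients, so enrolment may be over well before the decision can be made. Using the extension would then mean restarting recruitment, and the stated completion date could not hold.

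**Error rate.** The criterion concerns whether meaningful conclusions on the primary outcome are within reach. That appears to depend on the between-arm difference at the interim. If the final sample size depends on that difference, an ordinary two-sample test does not automatically keep its nominal level. How far it departs depends on the rule, and the protocol leaves the rule open. This matters even in a pilot, because the extension exists in order to reach statistically meaningful conclusions.

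**Working it through.** **Inputs, all from the protocol.** N = 120; accrual r = 7 to 8 per month; follow-up 12 months; interim at 80 completers; start 28 November 2020; last visit 28 February 2023, which is month 27.0. Accrual is taken as linear.

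**Reproducing the planned end date.** Last visit = 120/r + 12.
- r = 8: 15.0 + 12 = 27.0 months, which matches the stated date.
- r = 7: 17.1 + 12 = 29.1 months, about two months past it.

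The stated date therefore needs the top of the accrual range and has no slack.

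**Timing of the decision.**

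| Quantity | Formula | r = 8 | r = 7 |
|---|---|---|---|
| 120th patient recruited | 120/r | 15.0 | 17.1 |
| First 80 complete 12 months | 80/r + 12 | 22.0 | 23.4 |
| Gap after recruitment ends | 12 − 40/r | 7.0 | 6.3 |
| Left until planned last visit | 27.0 − (80/r + 12) | 5.0 | 3.6 |
| Earliest finish of a patient recruited after the interim | 80/r + 24 | 34.0 | 35.4 |

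In calendar terms, recruitment ends between about 27 February and 3 May 2022, and the interim falls between about 28 September and 11 November 2022. A patient recruited after it would finish at least 7.0 to 8.4 months beyond the planned last visit.

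The gap closes only if 12 − 40/r = 0, that is r = 3.33 per month. The earlier hospital-at-home trial cited under Power calculation recruited 118 in 18 months, or 6.56 per month; that rate still gives 12 − 40/6.56 = 5.9 months.

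**An earlier decision point.** The first 80 have 90-day data at month 80/r + 3, which is 13.0 (r = 8) or 14.4 (r = 7). That is 2.0 or 2.7 months before the 120th patient is recruited.

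**Error rate of an ordinary final test.** The level is assumed to be two-sided 5%. Let Z1 be the null z-statistic from the first 80 patients and W an independent standard normal for the rest. The final statistic is Z = [√80·Z1 + √(N − 80)·W]/√N, rejecting if |Z| > 1.96. No claim is made at the interim. Conditional power uses the interim trend, in whichever direction it lies. The first two rows come from 2,000,000 simulated trials and the third from numerical integration.

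| Extension rule | Cap on N | Type I error |
|---|---|---|
| Promising results only: conditional power at least 50% at the cap and below 80% at 120 | 160 to 360 | 4.7% to 4.8% |
| Whenever conditional power at 120 is below 80% | 160 to 360 | 5.6% to 6.4% |
| Worst case: N from 120 to the cap chosen to maximise rejection at every interim result | 240; 360 | 6.6%; 7.1% |

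The caps and conditional-power thresholds are illustrative; the protocol states none.

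**The case against.** **Details may be left to the SAP.** The significance level, a threshold and a maximum sample size are often specified there, and their absence from the protocol is not counted as an error here. That is accepted. What remains is fixed in the protocol itself: the trigger, the accrual rate, the follow-up and the end date, which do not fit together, and a criterion broad enough to admit rules both with and without inflation.

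**Reopening is possible.** This is also true. At the interim, patients 81 to 120 are still in follow-up and the final analysis has not been done. Reopening is awkward rather than impossible, but the protocol does not provide for it and its end date rules it out.

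**The likeliest reading may do no harm.** An extension made only when success looks achievable resembles the promising-results rule, for which no inflation was found. This limits the second difficulty. The level is not guaranteed, but it is not shown to be breached.

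Three stronger readings are tempting, and the document does not support them.
- *The interim is unblinded.* The protocol does not say so. Dependence on the between-arm result is an inference from the criterion, helped by the lack of any stated target difference on which a blinded decision could rest.
- *The error rate is 7.7%.* That is the result of testing at 5% at both 80 and 120 patients. The protocol does not state an efficacy test at 80.
- *The final estimate is biased upwards.* This depends on the rule. With a true effect of 0.3 SD and a cap of 240, extending whenever conditional power at the cap is at least 50% gives about +0.05 SD among extended trials but −0.03 SD over all trials. Extending whenever conditional power at 120 is below 80% gives about −0.03 SD among extended trials.

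**Conclusion.** The point holds and should be fixed, but it does not undermine the pilot.

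The timing conflict follows from the protocol's own numbers: the decision comes 6.3 to 7.0 months after the 120th patient is recruited and 3.6 to 5.0 months before the planned last visit. Any use of the extension takes the trial to month 34 or later instead of month 27. This assumes linear accrual at the stated rate. Visit windows and the length of the index stay move the gap by less than about half a month, and an SAP would not remove it.

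The error-rate part is conditional. With an assumed two-sided 5% level and no test at the interim, the final error lies between about 4.7% and 6.4% for the two rules examined, and at most 6.6% to 7.1% for caps of 240 to 360. The supportable statement is that 5% is not guaranteed. Since extension is optional and the main aim is to inform a definitive trial, this is a moderate weakness.

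**What to change.** Choose one of two routes and write it into the protocol before any interim data are seen. They should not be mixed: conditional power for a 12-month endpoint cannot be read directly from 90-day data, and a blinded decision cannot use a conditional-power zone.

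**Route A (preferred).** Take the decision when the first 80 patients have 90-day data (month 13.0 to 14.4), while recruitment is still open. Use only the blinded pooled SD and event rates, state a maximum N, and make no between-arm comparison. The ordinary final test can then stand. The costs are that blinded 90-day data are a less direct guide to the 12-month outcome, and that a target difference, which the protocol does not give, would have to be stated to turn an SD into a sample size. An extension would still move the end date, and this should be said.

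**Route B.** Keep the 12-month between-arm interim. State that no efficacy test is done at it, that the decision uses only the first 80 patients' outcomes, and that recruitment would be reopened. Reconcile the completion date and fix a maximum N. If the trial is extended, base the final test on an inverse-normal combination of the first 80 patients and the remainder, Z = √(80/120)·Z1 + √(40/120)·Z2, with these weights fixed now whatever the final N. This keeps the nominal level for any extension decision based on the first 80. The costs are a small loss of efficiency and a restart of recruitment.

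Either route is mainly a change of wording.

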### Randomisation

Patients will be randomly assigned 1:1 to the intervention or usual care. Independent stratified randomisation (via sealedenvelopes.com) using the PEARL score [25] (low, medium and high risk) and the presence of known CVD pre-hospital admission will be performed.

### Outcome measurements

Changes in the primary outcome between the intervention and usual care groups will be assessed using Student's t-test or Mann-Whitney U test. Time to first event (readmission or death) will be assessed using a Cox proportional hazards regression model. Changes in echocardiographic measurements between two time points will be assessed using paired Student's t-test or Wilcoxon signed-rank test. The relationship between undiagnosed / undertreated cardiac disease and outcome will be examined using logistic regression. In those surviving to the first follow up assessment, correlations between changes in right heart function and measures of COPD severity and exacerbation severity will be examined using bivariate comparisons appropriate to variable distribution. Mean change in QoL will be calculated by area under the curve per unit time; Student's t-test or Mann Whitney U will be used to compare this value between study arms.

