## Objectives

### Primary Objective

To assess the effect of comprehensive cardiovascular assessment and treatment on the primary endpoint to enable powering of a definitive multicentre RCT.

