## Study Endpoints

Key outcome measures of interest include readmission and mortality. Our primary outcome measure captures both readmission and death, reflects the number and duration of admissions, and places a higher weighting on mortality (particularly if soon after randomisation). To our knowledge this has not been used in a previous trial involving patients with COPD. Secondary outcomes are included to examine the utility of our novel primary outcome, and to gather important descriptive data to enable powering of the subsequent definitive RCT. Readmission, mortality and length of hospital stay will be collected from hospital health records, using Patient Administration System (PAS).

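### The primary comparison is an unadjusted t-test or Mann-Whitney test: it leaves out the randomisation strata and leaves open which of two different quantities is estimated

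*Protocol*

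**What the plan says.** The primary endpoint (Study Endpoints, Primary) is "The number of days spent alive outside of a hospital environment during 12 months post hospital discharge". The Study Endpoints section defends this choice partly because the measure "places a higher weighting on mortality (particularly if soon after randomisation"). The Primary Objective is to assess the effect on this endpoint "to enable powering of a definitive multicentre RCT".

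The Methods section describes "A randomised (1:1) pilot study of 120 consecutive consenting patients". Under Randomisation, allocation is stratified "using the PEARL score [25] (low, medium and high risk) and the presence of known CVD pre-hospital admission will be performed". That makes three PEARL levels by two CVD levels, or six strata.

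For the analysis, Outcome measurements says: "Changes in the primary outcome between the intervention and usual care groups will be assessed using Student's t-test or Mann-Whitney U test". It names no covariates or strata for this comparison, does not say when each test applies, and names no effect estimate to go with either test.

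**The concern.** There are two separate problems.

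- **Strata.** PEARL was built to predict readmission or death within 90 days, as the title of the protocol's own reference for the score says, and those events make up the primary endpoint. Balancing the arms on a prognostic factor reduces the true variance of the treatment difference. A two-sample test that ignores the factor still uses the full variance, so its standard error is too large and the precision gained by stratifying is not used.
- **Two tests, two quantities.** The t-test compares mean days. The Mann-Whitney test addresses the probability that a patient in one arm has more days than a patient in the other. On an endpoint bounded at about 365 days, with most survivors near the ceiling and a long tail of deaths, the two can give different answers. Only the mean difference in days directly carries the stated weighting on early death and serves as an input for sizing the next trial.

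At stake are some precision, a variance estimate for the definitive trial that is larger than it need be, and a primary result whose meaning depends on which test is used.

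**Working it through.** The protocol states no alpha, power, effect size or SD and says a power calculation is not possible, so there is no plan figure to reproduce. The check sizes the consequences.

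**Inputs from the protocol:** 120 patients at 1:1, so 60 per arm; six strata; the two named tests.

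**Assumed inputs:** two-sided alpha 0.05; no dropout; a true effect of 0.5 SD for the power comparison; R² is the share of outcome variance explained by the strata, taken over a range.

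**Step 1: cost of ignoring the strata.** With exact balance within strata and s = √(2/60) = 0.1826 SD units:

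- reported SE ÷ true SE = 1/√(1−R²)
- true alpha, unadjusted = 2Φ(−1.96/√(1−R²))
- power, unadjusted = Φ((0.5/s − 1.96)/√(1−R²)), where 0.5/s = 2.739
- power, adjusted = Φ(0.5/(s√(1−R²)) − 1.96)

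| R² | SE ratio | True alpha | Power, unadjusted | Power, adjusted |
|---|---|---|---|---|
| 0.05 | 1.026 | 0.044 | 0.79 | 0.80 |
| 0.09 | 1.048 | 0.040 | 0.793 | 0.819 |
| 0.10 | 1.054 | 0.039 | 0.79 | 0.82 |
| 0.20 | 1.118 | 0.028 | 0.81 | 0.86 |

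At R² = 0.09 the loss is 0.819 − 0.793 = 0.026, or 2.6 points of power. The variance that sizes an adjusted definitive trial, and so its sample size, is multiplied by (1 − R²), here 0.91.

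R² near 0.09 comes from a simulation of the endpoint with assumed event rates: control 12-month mortality about 23%, mean stay 6 days per readmission, SD about 104 days.

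A second simulation gave similar results. It assumed mortality about 25%, SD about 97 days and permuted blocks of four (the protocol gives no block size). With no treatment effect, the unadjusted reported SE was 17.8 days against an actual 17.2, and the t-test rejected in 4.3% of trials. Adjusting brought the reported SE to 16.8. With mortality multiplied by 0.6, power rose from 21.0% to 23.6%.

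**Step 2: what the rank test does to the mortality weighting.** In the first simulation's control arm:

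| Group | Mean days | Mean rank percentile |
|---|---|---|
| Death before day 90 | 38 | 0.04 |
| Later death | 202 | 0.17 |
| Survivor | 357 | 0.61 |

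Early deaths still rank lowest, so the order is kept. What shrinks is the distance: an early and a later death differ by 202 − 38 = 164 days but by only 0.13 in rank. Death explains 77% of the variance in days and 54% of the variance in ranks.

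**Step 3: whether the choice of test matters (60 per arm, same simulation).**

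| Assumed effect | Mean gain, days | Power, t-test | Power, Mann-Whitney |
|---|---|---|---|
| Mortality ×0.5 | 25.0 | 0.32 | 0.18 |
| Readmissions ×0.6 | 3.6 | 0.05 | 0.14 |
| Mortality ×0.6, readmissions ×1.5 | 15.9 | 0.15 | 0.05 |

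In the last row the probability of a better outcome on intervention is 0.495, although the mean gain is 15.9 days. The tests favour different kinds of benefit, and neither dominates.

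**The case against.** The strongest case on the other side has four parts.

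- **The strata effect is small.** This is an unpowered pilot, the unadjusted test errs on the safe side, and two to three points of power will not change its conclusions. This stands, and it limits the severity. It is not a reason to leave out factors already recorded at randomisation.
- **The t-test is named first and keeps both the days scale and the mortality weighting.** The rank problem arises only if Mann-Whitney is used. This also stands. However, an endpoint with a ceiling and a death tail will usually fail a normality check, so a choice based on distribution would tend towards the rank test.
- **Preferring the mean is partly a choice of estimand.** If the benefit is confined to readmissions, the rank test has more power (0.14 against 0.05 above). This is fair, and it is why a rank test should remain as a sensitivity analysis.
- **A statistical analysis plan, not shown here, may add a selection rule or an estimator.** It may. The protocol nevertheless fixes the pair of tests, and neither uses the strata.

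A reader might infer more than the documents support:

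- That the rank test discards the mortality weighting. It does not: early deaths keep the lowest ranks.
- That using Mann-Whitney would defeat the pilot's objective. Arm means, SDs and a difference in days can be reported whichever test is used, and nothing restricts the output to a p-value.
- That the open choice inflates type I error. That requires picking the test by its result, which the protocol does not say will happen.
- That the Cox model wrongly omits the strata. The protocol neither lists nor excludes covariates for it, so this can properly be left to an analysis plan.

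**Conclusion.** The point holds in a limited form and should be fixed. The protocol stratifies on two factors, at least one with a stated link to the outcome, and then fixes a primary comparison that uses neither. The result is a slightly conservative test and a modest loss of precision: alpha about 0.04 and 2 to 3 points of power if the strata explain about 9% of variance, with alpha from 0.044 to 0.028 over 5% to 20%. There is no bias and no inflation of type I error.

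The open choice between the tests also leaves the estimated quantity undefined. Of the two quantities, only the mean difference in days directly matches the reason given for the endpoint and the aim of powering a definitive trial.

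Every magnitude rests on assumed event rates, lengths of stay and R², none of which the protocol gives. The alpha range also assumes exact balance within strata; with incomplete blocks in six strata the effect would be somewhat smaller.

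**What to change.** In Outcome measurements, replace the two-test wording for the primary outcome with one analysis: the difference in mean days alive outside hospital, intervention minus usual care, from a linear model with arm, PEARL category (three levels) and known CVD (yes or no). Give a 95% confidence interval from robust standard errors or the bootstrap, because the endpoint is skewed and bounded. Report the residual SD alongside the arm means and SDs, so that the definitive trial can be sized for an adjusted analysis. Keep a van Elteren (stratified Wilcoxon) test as a sensitivity analysis.

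The cost is a change of wording; both factors are already recorded at randomisation. The one downside is less power than a rank test if the benefit is confined to readmissions, which the sensitivity analysis covers. The change should be made before outcome data are examined, ideally before the interim analysis planned after 80 patients have completed follow-up.

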## Hypothesis

A comprehensive, structured cardiovascular assessment, with treatment of problems identified, increases the time patients spend alive outside of hospital following hospital admission for a COPD exacerbation.

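### The primary outcome may be compared by t-test or Mann-Whitney, which have different targets on this outcome; no effect in days is named and the randomisation strata are not used

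*Protocol*

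**What the plan says.** The primary endpoint is "The number of days spent alive outside of a hospital environment during 12 months post hospital discharge". Under Study Endpoints the protocol justifies this choice partly on the ground that the measure "places a higher weighting on mortality (particularly if soon after randomisation"). The Hypothesis section states that the intervention "increases the time patients spend alive outside of hospital following hospital admission for a COPD exacerbation", and the primary objective is "To assess the effect of comprehensive cardiovascular assessment and treatment on the primary endpoint to enable powering of a definitive multicentre RCT".

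For the analysis, Outcome measurements says only: "Changes in the primary outcome between the intervention and usual care groups will be assessed using Student's t-test or Mann-Whitney U test". It gives no criterion for choosing, no effect measure and no confidence interval. The same paragraph does give a criterion, the distribution of the variable, for the right-heart correlations, but not for the primary outcome.

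The Randomisation section specifies "Independent stratified randomisation" by PEARL risk group (three levels) and by CVD known before admission. Neither factor appears in the primary comparison. The Power calculation section states no effect size or standard deviation, and looks to this trial for a treatment effect from which the definitive trial can be powered.

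**The concern.** Days alive outside hospital is bounded at about 365. Patients with few hospital days pile up near the top, and deaths form a long lower tail. On such an outcome the choice between the two tests is a choice of question. The t-test addresses the difference in mean days, in which a patient who dies on day 10 loses 355 days. Mann-Whitney addresses the probability that a patient in one arm does better than a patient in the other, in which only order counts.

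The hypothesis is about time, the stated rationale is the weight given to early death, and the objective is an input for sizing the next trial. All three point to a quantity in days, yet the wording allows a primary analysis that produces none. The open choice also carries into the Adaptive design section, where the decision to extend recruitment after 80 patients rests on conclusions about this outcome.

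Separately, randomisation is stratified by two factors that are plausibly prognostic, and the primary comparison ignores both.

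**Working it through.** The protocol has no figure of its own to reproduce, since it says that power cannot be calculated. The check is therefore a simulation plus simple arithmetic.

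**Inputs from the protocol.** 60 per arm (120 randomised 1:1); 43% readmitted within 90 days (Scientific Rationale). For 12-month mortality the protocol gives only an upper figure, up to 50% in the most unwell.

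**Assumptions.** Two-sided 5% level; 12-month mortality of about 25%; overdispersed (gamma-Poisson) readmissions. Set A: mean stay 7 days, 40% of deaths in the first 90 days. Set B: mortality 26%, median stay 4 days.

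**1. Shape.** Under set A the control arm has mean 294, median 343 and SD 103 days, so it is strongly left-skewed.

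**2. Weight on death (set A).**
- Days: death on day 10 costs 355 days. A survivor with 15 hospital days loses 15. The ratio is 355/15 = 23.7, about 24.
- Ranks: the same two patients lose 0.986 and 0.358 of the available rank range. The ratio is 0.986/0.358 = 2.8.
- Deaths (25% of patients) carry 77% of the variation in days but 42% of the variation in ranks.
- Deaths still rank lowest: mean percentile 0.15, against 0.62 for survivors.

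The weight is greatly reduced, not removed.

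**3. Power by type of effect.**

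| What changes | Set | Power, t | Power, Mann-Whitney |
|---|---|---|---|
| Deaths only, 26% to 14% | B | 27% | 19% |
| Deaths only, 25% to 12% (mean +26 days) | A | 34% | 22% |
| Same number of deaths, but later (90% v 0% of deaths in first 90 days; mean +39 days) | A | 51% | 11% |
| Admissions only, cut by 40% | B | 6% | 17% |
| Admissions only, halved (mean +9 days) | A | 8% | 30% |

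The t-test is the more sensitive when deaths change, above all when their timing changes. Mann-Whitney is the more sensitive when only admissions change. The set A contrasts kept their direction for mean stays of 5 to 10 days.

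**4. What the next trial needs.** For a difference in means, the 95% half-width is 1.96 × SD × √(2/60). At SD 100 this is 1.96 × 100 × 0.1826 = 35.8 days; at SD 60 and SD 130 it is 21.5 and 46.5 days. The next trial's size per arm at 80% power is 2 × (1.960 + 0.842)² × SD²/δ². For δ = 30 days this gives 63, 175 and 295 at SD 60, 100 and 130. Both steps need a difference in days and an SD. A Hodges-Lehmann shift added to Mann-Whitney would be in days, but it is a different quantity: about 4 days where the mean difference was about 27 (deaths 25% to 12%), and about 3 where it was about 42 (later deaths).

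**5. Strata.** If the strata explain a share R² of the variance, stratified allocation balances that share, but the unadjusted standard error still counts it. The inflation is 1/√(1 − R²): 1.054 at R² = 0.10 and 1.118 at R² = 0.20, so about 5-12% too large. Sizing the next trial from the unadjusted SD, if that trial also adjusts, inflates it by 1/(1 − R²), which is 11-25%.

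**The case against.** The strongest reply is that an analysis plan, not shown here, may fix the choice of test and the covariates, and that protocols commonly leave both to it. That stands in part: an analysis plan could cure this, so it is not a fatal flaw. But the protocol does more than stay silent. It names two tests with different targets, and a plan that chose Mann-Whitney would comply with it while sitting poorly with the protocol's own rationale and objective.

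Several stronger readings are tempting, and the documents do not support them.
- *Ranks remove the weight on death, or treat bed days as equal to dying.* They do not; deaths remain lowest and the earliest deaths lowest of all. The rationale also describes the outcome measure and promises nothing about a test, so this is a poor fit rather than a contradiction.
- *With Mann-Whitney the SD is unobtainable.* No test supplies an SD. Means and SDs by arm can be reported beside either one, and a rank-based trial can be sized from the probability of doing better. The protocol simply commits to none of these.
- *The tests will contradict each other in direction.* In a constructed scenario with fewer admissions but more deaths, estimated directions differed in about 29% of trials, but they differed in about 21% with no treatment effect at all. Most of this is sampling noise.
- *The type I error is inflated to 7-8%.* That needs a rule of taking whichever test is significant, which the protocol nowhere proposes. Each test alone holds about 5%.

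It is also fair to say that the unadjusted t-test is valid. Ignoring the strata makes it conservative, not anti-conservative. And preferring the mean difference has a price, shown in the admissions-only rows above.

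**Conclusion.** The point holds as a should-fix matter. The primary comparison is left between two tests with different targets, with no selection rule, no effect measure in days and no use of the stratification factors. Mann-Whitney greatly reduces the weight on early death (a ratio of about 24 in days becomes about 2.8 in ranks), and on its own it gives no difference in days for the hypothesis or for the aim "to enable powering of a definitive multicentre RCT".

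Power depends on the test and on what changes: about 27% against 19% for deaths only, and 6% against 17% for admissions only. Only the readmission rate and the sample size behind these figures come from the protocol. Mortality, timing of death and length of stay are assumed, so the sizes are illustrative. The pattern, not the exact percentages, is the finding. The 5-12% excess in the standard error likewise rests on an assumed 10-20% of variance explained by the strata.

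Pilot status does not remove the point, because estimating the effect on this outcome is the trial's primary objective. It does limit the severity: no confirmatory claim depends on the choice.

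**What to change.** Replace the sentence with one primary analysis, fixed before outcomes are compared by arm:
- the between-arm difference in mean days alive outside hospital, with a 95% bootstrap or robust confidence interval, from a linear model including PEARL risk group and known CVD;
- the SD by arm and the residual SD, reported for the definitive trial;
- Mann-Whitney kept as a labelled sensitivity analysis;
- days lost to death and days in hospital shown separately, so that a reader can see which component drives the result.

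The cost is one sentence of wording and no new data: both factors are already recorded for randomisation, and the protocol already plans bootstrapping for its skewed cost data. The downside is that the mean difference is less sensitive than the rank test if the intervention changes readmission days alone. The sensitivity analysis and the separate components cover that case.
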